## 2. OBJECTIVES

The overall objective: of this study is To evaluate the effect of 'culturally-sensitive hypertension Education"(CAHE) in Afro-Surinamese and Ghanaian patients who are treated in general practice for high blood pressure and have a blood pressure above target (systolic blood pressure (SBP)> 140 mmHg and / or diastolic blood pressure (DBP)> 90 mmHg).

The specific objectives are:

Primary specific objective:

1. To determine if there are significant differences in the reduction in systolic blood pressure between the intervention group (patients who have received CAHE) and the control group after eight months past baseline.

Secondary specific objectives:

2. To evaluate whether, whether there are significant differences in the degree of medication adherence between the intervention group (patients who have received CAHE) and the control group at 8 months past baseline.

3. To evaluate whether there are significant differences in the adherence to lifestyle advice between the intervention group (patients who have received CAHE) and the control group, at 8 months past baseline.

4. Furthermore, a process evaluation will be carried out that includes the following questions are discussed:

- Is it feasible engage patients of the ethnic monotity groups in question in a culture-sensitive education program? And there are differences in participation and feasibility between subpopulations (eg, by ethnic origin, gender, age, education)?

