**Main study parameters / endpoints:** Primary outcome measure is the measured systolic blood pressure at baseline minus the systolic blood pressure after 8 months (blood pressure is electronically measured twice, for sitting patients after 15 minutes of rest, the average of the two measurements is recorded.). Secondary outcomes are changes after 8 months in the degree of adherence to medication and lifestyle advice; mediating factors that may influence how patients deal with hypertension: (beliefs about hypertension and medication / lifestyle changes, motivation for medication use and lifestyle changes, perceived self-efficacy to use medication/carry out lifestyle changes and satisfaction with care.

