### 3. STUDY DESIGN

The study is designed as a cluster-randomized controlled trial (RCT), which will compare patients who receive CAHE and with those who only receive usual care. We will collect data on the level of the patient, but randomize at the level of health care centres. The main reason for choosing a RCT with cluster randomization instead of a RCT with randomisation at patient level is that with the latter study design contamination can easily occur between the intervention and control groups.

On the basis of an analysis of numbers of patients, four health care centers (clusters) are required for this study, two for the intervention arm and two for the control arm. Important selection criteria for health care centers are that they should treat a sufficient number of patients from the target groups and that the hypertension care takes place according to the NHG standard CVRM.

The four health centers participating in the study will be randomly assigned to the intervention arm or the control arm (1 to 1 ratio).

The randomization will be performed by an employee of the Data Management Services team of the KEBB department of the AMC who is not involved in the study and blinded to the identity of the practices. In the health centers that are assigned to the intervention arm enrolled patients will get the CAHE. In the health centers that are assigned to the control arm enrolled patients will get the usual care which is provided in the health care centers. It is assumed that intercluster variance will be low. Based on the inclusion criteria and the fact that patients are treated with the same standard NHG in all four centers, we assume that differences in the mean blood pressure of hypertensive patients from the four centers will be low. Because the intra-cluster correlation coefficient is a ratio of the low between cluster variation and the within cluster variation, the intra-cluster correlation (ICC) is estimated to be <3%.

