#### **6.1.2. Secondary study parameters / endpoints (if applicable)**

Difference between baseline and 8 months past baseline regarding the following measures:

- Adherence to medication
- Adherence to lifestyle advice
- Mediating factors that may affect the way in which patients manage hypertension:
  - o beliefs about hypertension and medication / lifestyle changes
  - o motivation to use / medication to carry out lifestyle changes
  - o self-efficacy to use / medication to implement lifestyle changes
- Satisfaction with care
- Baseline demographics of potential confounders, such as age, gender, ethnicity, environment and other socio-economic circumstances are included in the study.

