### **8.2 Univariate analysis**

Analysis of the primary outcome data: the systolic blood pressure measured at baseline minus the systolic blood pressure measured at 8 months past baseline.

All data entries will be controlled at random to avoid potentially incorrect codings. Univariate analyses will be conducted on the corrected database to compare variable distributions and identify positive or negative outliers. The analysis of the primary outcome measures will be carried out according to the 'intention to treat' principle. The primary outcome measure is calculated for each patient. Then the average within-group difference will be calculated for patients in the intervention group and the control group. Subsequently, the between-group difference between the calculated within-group differences will be calculated with a corresponding confidence interval. A decrease in systolic blood pressure by 10 mmHg (standard deviation = 15) in the intervention group as compared to the control group, with a confidence level of 5% probability of a Type 1 error, is considered to be clinically relevant. The analysis will use univariate and adjusted multilevel analysis.

The secondary data are analyzed in the same way.

If possible, separate subgroup analyses will be carried out by ethnic group and gender. For all analyses, a p value of 0.05 is used as the critical value. In subgroup analyses will be an adjustment to the p value for the number of analyses performed.

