### **8.3 Multivariate analysis**

Differences in the blood pressure values between treatment arms will be analyzed using a mixed model regression analysis that will take the dependence of the data and the intraclass correlation between centers into account. Corrections will also be performed for any differences in baseline characteristics of patients between the treatment arms.

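### Objectives 2 and 3 ask for a between-arm difference in adherence at 8 months, while the endpoint and analysis sections use change from baseline, and baseline adherence is not named as a covariate

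*Protocol*

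**What the plan says.** Section 2 of the protocol, repeated in the Summary, lists three effectiveness objectives. The first is about change: "significant differences in the reduction in systolic blood pressure between the intervention group" and control. The second and third are worded as differences at the 8-month point: "differences in the degree of medication adherence between the intervention group (patients who have received CAHE) and the control group at 8 months past baseline" for medication, and "significant differences in the adherence to lifestyle advice between the intervention group" and control for lifestyle advice.

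The endpoint text is worded as change. The Summary (main study parameters / endpoints) has "Secondary outcomes are changes after 8 months in the degree of adherence to medication and lifestyle advice". Section 6.1.2 introduces the secondary endpoints, adherence among them, with "Difference between baseline and 8 months past baseline regarding the following measures".

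Section 8.2 forms each patient's baseline minus 8-month value, averages it within arm and compares the arms. It mentions univariate and adjusted multilevel analysis, and then adds: "The secondary data are analyzed in the same way".

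Section 8.3 describes a mixed model for blood pressure values that allows for correlation within centres. It continues: "Corrections will also be performed for any differences in baseline characteristics of patients between the treatment arms". The baseline adherence score is not mentioned.

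Section 3 fixes the design: "four health care centers (clusters) are required for this study, two for the intervention arm and two for the control arm".

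**The concern.** In one short list, the protocol words objective 1 as a reduction and objectives 2 and 3 as a state at 8 months. Read literally, the question asked about adherence is not the one that the endpoint and analysis sections answer, and no section reconciles them.

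The distinction has no effect on the treatment estimate if the baseline score is a covariate in a linear model. It does have one if raw contrasts are compared, because a chance difference in baseline adherence enters the change contrast with the opposite sign. Adherence is the behaviour that the intervention is meant to alter, so the report should leave no doubt about which contrast answers objectives 2 and 3.

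**Working it through.** **Inputs.** From section 4.4: 60 evaluable patients per arm and 30 per centre. From section 3: two centres per arm. From sections 3 and 4.4: ICC below 3%, argued from blood pressure. The documents give no ICC, SD or baseline-to-8-month correlation for adherence. Results are therefore in patient-level SD units, with the ICC varied from 0 to 0.10 and the correlation r from 0.3 to 0.7, both as assumptions.

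**The plan's own figure.** The protocol has no sample-size figure for adherence. The blood pressure figure supplies the 60 and the 30, and it reproduces. With two-sided 5% (sidedness is not stated), 80% power, a difference of 10 and SD 15, the requirement is 35.3 per arm before clustering. Multiplied by 1 + 29 × ICC, this reaches 60 at an ICC of about 0.024, inside the stated bound. Then 120 / (1 − 0.5) = 240.

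**Gap between the two unadjusted definitions.** Let D8 and D0 be the between-arm differences in mean score at 8 months and at baseline, in the same patients. The level contrast is D8 and the change contrast is D8 − D0, so they differ by exactly D0. Under randomisation D0 has mean zero and

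SD(D0) = sqrt[ (2/60) × (1 + 29 × ICC) ].

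| ICC | 1 + 29 × ICC | SD(D0) | P(gap above 0.25 SD) |
|---|---|---|---|
| 0 | 1.00 | 0.18 | 0.17 |
| 0.01 | 1.29 | 0.21 | 0.23 |
| 0.03 | 1.87 | 0.25 | 0.32 |
| 0.10 | 3.90 | 0.36 | 0.49 |

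In variance terms the gap is 2/60 = 0.033 at ICC 0 and 0.033 × 1.87 = 0.062 at ICC 0.03. So 1/1.87 = 53% of the variance at ICC 0.03 would be present with no clustering at all.

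**Precision.** Take a roughly continuous score with equal variance at both times. Relative to the variance of the 8-month score, the change has variance 2(1 − r), and the 8-month score adjusted for baseline has 1 − r².

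| r | Change, 2(1 − r) | Adjusted, 1 − r² |
|---|---|---|
| 0.3 | 1.40 | 0.91 |
| 0.5 | 1.00 | 0.75 |
| 0.7 | 0.60 | 0.51 |

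The difference 2(1 − r) − (1 − r²) equals (1 − r)², which is never negative. The adjusted variance also never exceeds 1, that of the raw level.

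**Equivalence after adjustment.** With the T0 score as a covariate in a linear model, replacing the 8-month score by change only shifts the coefficient of the T0 score by 1. The treatment coefficient is unchanged. A numerical check with 60 simulated patients per arm gave 0.517 for both outcomes.

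**The case against.** The strongest reply is that the operative definition can already be found. The Summary endpoints, section 6.1.2 and section 8.2 all point to change, and only the objectives are worded more loosely. This stands, and it limits the severity. A reader might infer that the trial could claim success on whichever definition looks better. The documents do not support that, because the analysis section commits the secondary data to the primary outcome's method.

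A second reply is that section 8.2 plans an adjusted multilevel analysis and section 8.3 corrects for baseline differences, so an unadjusted gap may never reach the report. This stands in part. The detailed covariate list may properly sit in a statistical analysis plan that is not at hand. As written, however, section 8.3 concerns blood pressure values and does not say that the T0 adherence score is among the covariates.

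A third reply concerns size, and it also stands. The ICC bound is argued from blood pressure in patients selected on blood pressure, so it need not hold for adherence. It would be wrong to say that the four-centre design creates the gap: at ICC 0 its SD is still 0.18. A reader might also set 0.25 SD against the primary effect of 10/15 = 0.67 SD, but no target effect is given for adherence, so that comparison says nothing about adherence conclusions.

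**Conclusion.** The inconsistency is real: objectives 2 and 3 describe a difference at 8 months, whereas the endpoint and analysis text describes change. For unadjusted contrasts the two differ by the baseline arm difference, with an SD of about 0.18 patient-level SD at ICC 0 and 0.25 at ICC 0.03. At ICC 0.03 the gap exceeds 0.25 SD in about 32% of trials of this size. These figures assume 30 evaluable patients in each of four centres, a blood-pressure ICC applied to adherence, and the same patients in both contrasts. The precision comparison further assumes r of 0.3 to 0.7 and a score that can be treated as continuous; it does not carry over to refill adherence classified as adherent or not.

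Severity is minor to moderate, since these are secondary endpoints and three places already agree on change. The correction is still worth making: it removes the ambiguity and replaces a raw change contrast with one that, under the assumptions above, is never less precise.

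**What to change.** Use one definition of the self-reported adherence outcomes in the Summary (objectives and endpoints), section 2, section 6.1.2 and the secondary-data sentence of section 8.2. State that the effect is the between-arm difference in the 8-month self-reported adherence score, estimated in the centre-level mixed model with the same score at T0 as a covariate. Note that using change as the outcome in that model gives the same treatment estimate. Raw change by arm can be reported descriptively.

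State separately how pharmacy refill adherence (section 6.3, Medication Use) is compared. No baseline window is given for it, so change from baseline is undefined for that measure.

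Merely adding the idea of change to objectives 2 and 3 would cure the contradiction, but would leave the T0 adherence score unnamed in the model. The fuller fix does alter the stated secondary contrast, so section 8.2 must be amended with the rest. It needs no new self-report data, because the interview in section 6.3 collects the scores at both T0 and post-test. The refill comparison may need a baseline period of pharmacy data if change is wanted there.

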### 3. STUDY DESIGN

The study is designed as a cluster-randomized controlled trial (RCT), which will compare patients who receive CAHE and with those who only receive usual care. We will collect data on the level of the patient, but randomize at the level of health care centres. The main reason for choosing a RCT with cluster randomization instead of a RCT with randomisation at patient level is that with the latter study design contamination can easily occur between the intervention and control groups.

On the basis of an analysis of numbers of patients, four health care centers (clusters) are required for this study, two for the intervention arm and two for the control arm. Important selection criteria for health care centers are that they should treat a sufficient number of patients from the target groups and that the hypertension care takes place according to the NHG standard CVRM.

The four health centers participating in the study will be randomly assigned to the intervention arm or the control arm (1 to 1 ratio).

The randomization will be performed by an employee of the Data Management Services team of the KEBB department of the AMC who is not involved in the study and blinded to the identity of the practices. In the health centers that are assigned to the intervention arm enrolled patients will get the CAHE. In the health centers that are assigned to the control arm enrolled patients will get the usual care which is provided in the health care centers. It is assumed that intercluster variance will be low. Based on the inclusion criteria and the fact that patients are treated with the same standard NHG in all four centers, we assume that differences in the mean blood pressure of hypertensive patients from the four centers will be low. Because the intra-cluster correlation coefficient is a ratio of the low between cluster variation and the within cluster variation, the intra-cluster correlation (ICC) is estimated to be <3%.

## **4. STUDY POPULATION**

### **4.1 Population (base)**

#### **Practices**

A total of 240 patients who are diagnosed with hypertension and meet the inclusion criteria will be recruited from the participating general practices (health care centers). It is expected that the following practices will participate in the study: two GAZO-centers: "Reigersbos" and "Klein Gooioord" and two other centers in the 'high Bijlmer' neighborhood. We choose these practices because they are located in a region where relatively many Afro-Surinamese and Ghanaians are living. The first two centers that are part of the GAZO foundation (Healthcare centres Amsterdam South East), have an estimated number of 401 Afro-Surinamese and 75 Ghanaian patients with hypertension (K86 + K87). As other health care centers, 75 in Amsterdam South East we are considering Kraaiennest and a center to be determined). The latter two centers are located in the "high Bijlmer", the neighbourhood where the with the highest number of Ghanaian and Surinamese population in Amsterdam South East. Based on data from the SUNSET study, (6) we assume that about 63% of the patients who are treated for HTN will have a BP above the target values ( $\geq 140/90$  mm Hg at two measurements)

### **4.2 Inclusion criteria**

Patients will be included if they meet the following criteria: Afro-Surinamese or Ghanaian (according to self-identification), older than 20 years, according to the electronic patient record diagnosed with hypertension (K86, K87), a blood pressure higher than the target values (systolic blood pressure (SBP)  $> 140$  mmHg and / or diastolic blood pressure (DBP)  $> 90$  mmHg)

### **4.3 Exclusion criteria**

Patients will be excluded if they have Diabetes Mellitus type 1 or 2 diabetes. The reason is that many diabetic patients with BP are following diabetes education programs and such programs may overlap with parts of the intervention we offer in this trial. Furthermore, patients are excluded from participation, if they participate in other CVD trials or if the treating physician considers the patient not suitable for participation (eg due to existing comorbidities)

### **4.4 Sample size calculation**

Four health care centers will be needed for the study and cluster-randomization. We assume a low between-cluster variance because of the homogeneity of demographic characteristics of the patient populations and treatment approaches of the participating health care centers. Based on the inclusion criteria and the fact that patients are treated according to the same clinical guideline (NHG), we assume little variation between the average blood pressures of hypertensive patients with an inadequately controlled BP. Because the intra-cluster correlation coefficient (ICC) is a ratio of the low between-cluster variation and within-cluster variation, we assume an ICC of  $< 3\%$ . The primary outcome measure will be a decrease in SBP at 8 months. A decrease of 10 mmHg (standard deviation = 15) in the intervention group compared to the control group will be considered as clinically relevant. To demonstrate this difference statistically with a reliability of the 5% chance of Type 1 error and a power of 80%, an average cluster size of 30 patients per cluster (health care centre) is needed. We strive to recruit a total 120 patients: 60 patients per treatment arm. Assuming an average dropout rate of 50%, 240 participants will have to be recruited.

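### The 80% power in section 4.4 ignores that only four centres are randomised: with inference on 2 degrees of freedom it is about 33% at ICC 3% and 50% at ICC 0

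*Protocol*

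**What the plan says.** Protocol section 4.4 takes as its target "A decrease of 10 mmHg (standard deviation = 15) in the intervention group compared to the control group". It sets a "5% chance of Type 1 error and a power of 80" per cent, and concludes that with "a power of 80%, an average cluster size of 30 patients per cluster (health care centre) is needed". The analysed number is then fixed: "We strive to recruit a total 120 patients: 60 patients per treatment arm". Recruitment is doubled to 240 to allow for 50% dropout.

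Section 3 gives the design: "four health care centers (clusters) are required for this study, two for the intervention arm and two for the control arm". Section 6.2 repeats that whole centres are randomised, two to each arm. On clustering, section 3 says "the intra-cluster correlation (ICC) is estimated to be <3" per cent, and section 4.4 repeats that bound. No point value for the ICC is given anywhere.

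For the analysis, section 8.2 says "For all analyses, a p value of 0.05 is used as the critical value" and plans a between-group difference with a confidence interval. Section 8.3 plans a mixed model that allows for correlation within centres. Neither section states the reference distribution or whether the test is one- or two-sided.

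**The concern.** The unit of randomisation is the centre, and there are four. The comparison of arms therefore rests on two centre means against two, and the variation between centres within an arm has to be estimated from 4 − 2 = 2 degrees of freedom. The two-sided 5% critical value is then 4.30, not 1.96. Section 4.4 allows for clustering through an ICC but says nothing about this loss. When there are many clusters the omission hardly matters. With two per arm it dominates.

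The power statement is the only quantitative justification for the size of the trial. If true power is well below 80%, a real 10 mmHg effect could easily be missed, and a reader who trusts the 80% would give a non-significant result more weight than it can bear.

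**Working it through.** **Inputs.** Difference 10 mmHg, SD 15, type I error 5%, power 80%, 30 analysed per centre and 60 per arm (section 4.4); two centres per arm (sections 3 and 6.2); ICC below 3% (sections 3 and 4.4). Assumptions: the test is two-sided, and SD 15 is the standard deviation of the change in systolic pressure.

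**1. Reproducing the stated figure.**
- Without clustering: n per arm = 2 × (15/10)² × (1.96 + 0.8416)² = 35.3.
- Design effect with 30 per centre: DE = 1 + 29 × ICC.
- Setting 35.3 × DE = 60 gives ICC = (60/35.3 − 1)/29 ≈ 0.024. So 30 per centre gives 80% under the normal formula if the ICC is about 2.4%, and more than 80% below that.
- At ICC 3%: DE = 1.87 and SE = √(2 × 225 × 1.87/60) = 3.74 mmHg. The ratio 10/SE is 2.67 and normal-formula power is 76%.
- Dropout: 120/(1 − 0.5) = 240, which is correct.

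The 80% therefore comes from a normal reference with an ICC that the protocol does not name.

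**2. Centre as the unit, 2 df.** SE = √(2 × 225 × DE/60); noncentrality = 10/SE; critical t on 2 df = 4.303; power from the noncentral t distribution. The half-width is 4.303 × SE, evaluated at the planning SE.

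| ICC | DE | SE (mmHg) | 10/SE | Power, normal formula | Power, 2 df | 95% CI half-width (mmHg) |
|---|---|---|---|---|---|---|
| 0 | 1.00 | 2.74 | 3.65 | 95% | 50.4% | 11.8 |
| 1% | 1.29 | 3.11 | 3.21 | 90% | 42.6% | 13.4 |
| 2% | 1.58 | 3.44 | 2.90 | 83% | 37.0% | 14.8 |
| 3% | 1.87 | 3.74 | 2.67 | 76% | 32.9% | 16.1 |

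A simulation with 400,000 replicates gave 50.4% at ICC 0 and 33.0% at ICC 3%, in agreement. The difference detectable with 80% power on 2 df is about 15.5 mmHg at ICC 0 and 21 mmHg at ICC 3%.

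**3. What more patients in the same four centres would do.** With unlimited patients per centre, SE tends to √(2 × 225 × ICC/2).
- ICC 3%: SE → 2.60, power at most about 54%.
- ICC 2%: SE → 2.12, at most about 68%.
- ICC 1%: SE → 1.50, at most about 89%.
- ICC 0: no ceiling.

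If all 240 recruits were analysed (60 per centre), power would be 40.6% at ICC 3% and 74.1% at ICC 0.

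**4. More centres, still 30 per centre.** With df = 2(k − 1) for k centres per arm, power at ICC 3% is 69% for three per arm and 88% for four. At ICC 0 it is 91% for three per arm.

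**The case against.** **The ICC is below 3%, not equal to it.** This stands. A reader might infer an arithmetic error from the 35.3 × 1.87 = 66 per arm needed at 3%, against 60 planned. The documents do not support that: an ICC of 2.4% lies inside the stated range and returns 60 per arm. What remains is that the value used is not stated and that power is 4 points short at the bound.

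**The degrees-of-freedom method may be left to the statistical analysis plan.** True, and its absence here is no fault. The 33% to 50% range is conditional on 2-df inference. But a later choice of method cannot add centres. A simulated mixed-model Wald test with a normal reference had power of about 74% at ICC 3%, but a type I error of about 9%, above the 5% in section 4.4. At ICC 0 that test kept its level (about 4%) with power of about 89%, so the 80% could be defended if the ICC were in fact zero. The protocol does not assume that, and four centres could not confirm it.

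**Sidedness is not stated.** A one-sided 5% test on 2 df gives 54% at ICC 3% and 75% at ICC 0, still short of 80%.

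**Baseline adjustment may reduce the SD.** Possibly, but the protocol gives no correlation or reduced SD from which to credit it.

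**More patients would help.** Partly right. A reader might infer that adding patients in these centres is useless. That does not follow: the ceiling of about 54% applies at ICC 3%, while near ICC 0 larger centres raise power substantially.

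**Nothing says a null result will be read as no effect.** Correct; section 8.2 already promises a confidence interval. The risk lies in the 80% claim itself, not in a stated rule of interpretation.

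**Conclusion.** The point holds as a fault in the design justification, not as a slip in arithmetic. The claimed 80% depends on a large-sample formula that is not appropriate for two centres per arm. Under centre-level inference on 2 df, power for 10 mmHg is roughly a third at the upper ICC bound and about a half at ICC 0, so no value in the protocol's own range brings it near 80%. At ICC 3% the interval half-width of about 16 mmHg is wider than the effect sought.

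These figures assume a two-sided 5% test, SD 15 for the change score, equal centres of 30 analysed patients, and between-centre variance estimated from the four centres. The number of centres is the main limit. Patients per centre are a further limit when the ICC is close to zero.

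**What to change.** In section 4.4:
- Replace the 80% statement with power for 10 mmHg at 60 analysed per arm: about 33% at ICC 3%, 37% at 2%, 43% at 1% and 50% at 0, each labelled with its ICC and as two-sided 5% inference on 2 df.
- State the ICC value used in the calculation, not only its upper bound.
- Give the 95% confidence interval half-width: about 12 mmHg at ICC 0 and 16 mmHg at ICC 3%.
- Say that the small number of centres is the main limit: at ICC 3% power stays at or below about 54% however many patients each centre adds, while at ICC near 0 more patients per centre would also raise it.
- Say that a non-significant result will be reported as an estimate with its interval, not as absence of effect.

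The cost is protocol wording and a less favourable stated power. If the sponsor wants to keep an 80% target on 2-df-type inference across the whole ICC range with 30 analysed per centre, the calculation above points to four centres per arm. That is a larger change to the design and is not needed to correct the text.
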